##### Outcome Measurements

The questionnaire for the healthy parents includes the information shown in Textbox 2. The questionnaire to the children includes the information shown in Textbox 3. The questionnaire set to the network members includes the information shown in Textbox 4.

Information included in the questionnaire for the healthy parents.Demographic data about the healthy parent: age, gender, education, social status, children, employment status, and income.Demographic and medical data about the sick parent: age, gender, type and degree (metastasis) of cancer, months since diagnosis, type of treatment, and months of treatment and current treatment status.The Crisis Support Scale (CSS) [48] and the Assistance Questionnaire-Receivers of support (AQR) [49] measure social support. CSS is a short scale for measuring social support after a crisis has occurred, consisting of 7 questions with a rating scale from 1 (never) to 7 (always). All items are summed for a total mean score, where a higher total score indicates more received support. The scale appears to be very robust and to have satisfactory psychometric properties [48]. AQR measures adults’ experiences and need for 9 different types of social support related to the situation caused by the cancer. The instrument was developed by Dyregrov et al [49] and is applied on comparable populations both nationally and internationally.The Quality of Life Scale (QOLS-N) is used to measure the healthy parent’s quality of life [50]: This instrument measures an individual’s overall satisfaction with life based on different life domains. It contains 16 items scored on a 7-point Likert scale ranging from “very satisfied” to “very dissatisfied”. The items are calculated into the 6 subscales to assess satisfaction with life domains. The dimensions are scored by summing the scores for each item in the subscale. Possible total scores range from 16-112, where a lower score indicates worse quality of life demonstrated satisfactory psychometric properties in several studies [50,51]. The 6 subscales are as follows: (1) physical and material well-being; (2) personal development; (3) relationships with others; (4) participation in social activities; (5) participation in community and civic activities; and (6) recreation.The General Health Questionnaire (GHQ-12) is used to assess current mental health and psychological distress, reflecting the inability of normal functioning in regard to distressing experiences [52]. The questionnaire consists of 12 items on a Likert scale ranging from 0 to 3, where a higher sum-score indicates more symptoms of psychological distress and worse mental health. The GHQ-12 is widely used as a reliable screening instrument for psychological distress and minor psychiatric morbidity outside a clinical setting, showing high psychometric properties in various populations [52].The Self- Efficacy Parent Task - Short Form (SEPTI-SF) is used to measure 2 dimensions of the parent’s self-efficacy, discipline and achievement, showing satisfactory psychometric properties [53]. These dimensions consist of 11 quotes with 6 alternative answers from “highly disagree” (1) to “highly agree” (6). The dimensions are scored by summing the scores for each item in the subscale.The Dispositional Resilience Scale-Revised (DRS-15-R/Hardiness) is used to assess the parents’ hardiness in meeting challenging life events and situations [54]. The questionnaire consists of 15 quotes with 4 alternative answers scored on a Likert scale ranging from “highly disagree” (0) to “highly agree” (3). The items are summed into the 3 dimensions, commitment, challenge, and control, where a higher score indicate higher hardiness. The instrument is used internationally as well as in Norway, and has demonstrated validity and reliability within a wide range of studies as well as sensitivity to change [54].

Information included in the questionnaire to the children.Demographic data: age, gender, siblings, and grade in schoolThe Revised Child Manifest Anxiety Scale (RCMAS) is used to measure anxiety reactions in children [55]. The RCMAS consists of 28 anxiety items and 9 lie (social desirability) yes-or-no items. Sum scores are provided for total anxiety and the 4 sub-scales: worry/oversensitivity, physiological anxiety, social concerns/concentration and a lie scale. A higher score indicates higher levels of anxiety or lie. RCMAS has demonstrated adequate psychometric properties [55].Kinder Lebensqualität (KINDL) is used to assess the quality of life of children [56]. KINDL consists of 30 quotes with 4 alternative answers ranging from “never” to “always”. The 6 subscales (physical health, emotional well-being, self-esteem, family, friends, and school) are calculated, where higher scores indicate higher QOL. The questionnaire has showed psychometrically acceptable values [56]. KINDL has 3 versions related to age, but since these cover the exact same questions with somewhat different wording, we decided to use Kid-KINDL to cover the entire age-span.

Information included in the questionnaire to the network.Questionnaire informationDemographic data: age, gender, education, social status, work affiliation, and relation to the family/sick parent.Assistance Questionnaire: Providers of support (AQP) represents the opposite version of AQR as it measures the social support given.GHQ-12, QOLS-N, Hardiness and CSS, as described for the healthy parents.

##### Data Collection

Healthy parents and the children fill out the entire dataset at inclusion (T1), after 3 months (approximately one months after the intervention for the intervention group), and after 6 months (Figure 2). One of the two first authors provides the families with questionnaires by post and they return them to the researchers in pre-stamped envelopes. The social network members in the intervention group fill out the T1 questionnaires prior to the meeting starting. The network members in the intervention group fill out the same questionnaires after 3 (T2) and 6 months (T3), distributed via the Internet and the website SurveyMonkey.

##### Power Calculations and Statistical Analyses

When comparing differences between the intervention group (n=30) and the control group (n=30), the power analysis showed that with *P*<.05 and a statistical power = .80, one would be able to detect effect sizes of *t* tests of about 0.65 of one standard deviation or higher [46]. This means an ability of detecting effects sizes of medium size or higher according to Cohen’s criteria [46]. This effect level was judged to be of clinical interest, and was within the study’s recruitment frame and economy.

All the data will be coded, verified, and entered into IBM SPSS Statistics for Windows Version 22.0. Normality will be assessed through examinations of skewness and kurtosis for all variables. A two-tailed *P* value of <.05 is considered to be statistically significant [46,57]. Descriptive statistics (mean/median or percentages, SD, and ranges) and correlation analyses (Pearson correlation) will be used to describe the data and to explore relationships among them [57]. The outcome variables will provide sum-scores on the interval level. Multiple regression analysis will be used to explore directional relationships among variables and testing the research model. For the estimation of the effect and the relationships of the variables relevant to the intervention, different methods such as *t* tests and structural equation (SEM) analyses will be used [57]. The missing data problem will be analyzed according to the questionnaires’ manual. Statistics will be reported in line with the SAMPL guidelines stated by Lang and Altman [58].

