### Eligibility Criteria

The study contains 3 samples. Sample 1 and 2 (n=60) consist of 30 families in the intervention group and 30 in the control group. These samples include the healthy parent and one child from each family. The inclusion criteria for these families are (1) a healthy parent having a partner or spouse diagnosed with cancer within the last five years and treated for cancer and (2) one child in every family, aged 8-18 years old, living with a parent who has cancer. With multiple children in the family, the oldest child who is willing to participate will be recruited. The parents in the intervention group ask the number of adult network members (mean 7, limited to 15 network members, N=210) if they want to participate in the intervention. This group of adult network members makes up Sample 3. The inclusion criteria for these network members are (1) extended family members, friends, neighbors, and work colleagues of the parents, (2) ≥18 years, and (3) living nearby the family.

The exclusion criteria for the study are (1) healthy parent not living with the ill parent or the ill parent has died, or having a serious disease, (2) children <8 years old, not living with ill parents, serious disease themselves, and (3) network members living >2 driving hours from the family.

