#### Ethical Implications and Risk

The Regional Committee of Research and Ethics in Western (REK West) Norway and the Norwegian Social Science Data Services (NSD) approved the research protocol October 9, 2013 (reference number: 2013/1491/REK vest).

The study will be conducted in compliance with the Declaration of Helsinki [59] and the requirements for data processing outlined in the NSD [60]. Only the two first authors have access to the data files. Procedures for handling data and data security in the study are developed. Study participation is based on written and oral information and written consent [59]. For children <12 years of age, the parents must consent on behalf of the children, whereas for the 12-18 year old children the consent is given from both parts. Study participation is voluntary and participants can withdraw at any time without the provision of reasons or any negative consequences. Serious risks or undesired effects of the intervention or the assessment by questionnaires are not described in the literature and no specific risks related to this study are anticipated. All the professionals participating in the study have extensive experience as researchers or clinicians in the field of working with children, serious illness, crisis, grief, and trauma. This competence will secure ethical and safe conditions for the participants. A referral process for further assistance or treatment for participating families with special needs will be ensured by the psychologist. Any changes in the study protocol will be applied for to REK West and NSD.

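### The stated .80 power at about 0.65 SD is about 0.70 under the article's own two-tailed test even with all 60 families retained, and nothing is allowed for loss by 6 months

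*Protocol article*

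**What the plan says.** The section Power Calculations and Statistical Analyses opens: "When comparing differences between the intervention group (n=30) and the control group (n=30), the power analysis showed" that, at P<.05 and with "a statistical power = .80, one would be able to detect effect sizes of" t "tests of about 0.65 of one standard deviation or higher". It adds that this level was considered clinically interesting. The Abstract repeats the 30 v 30 comparison and the .80, without the effect size.

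The same section sets the test level: "A two-tailed *P* value of <.05 is considered to be statistically significant". For the intervention effect, "different methods such as *t* tests and structural equation (SEM) analyses will be used".

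The recruited sample is given under Eligibility Criteria: "Sample 1 and 2 (n=60) consist of 30 families in the intervention group and 30 in the control group". Samples 1 and 2 are the healthy parents and the children, one of each per family.

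Outcomes are collected at inclusion (T1), 3 months (T2) and 6 months (T3). On the method, Data Collection says: "One of the two first authors provides the families with questionnaires by post and they return them to the researchers in pre-stamped envelopes". Under Ethical Implications and Risk, "participants can withdraw at any time without the provision of reasons or any negative consequences". Missing data are referred to the questionnaires' manual. The article states no expected loss rate and no inflation of the sample.

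**The concern.** The number entering the power analysis is the number recruited. Trial Design places allocation after T1 is returned, so an effect of the program can show only at T2 or T3. A t test at those times uses only the families who returned that questionnaire. The stated sensitivity therefore has no margin for loss.

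Checking the figure shows a second and separate problem. The 0.65 SD does not follow from 30 v 30, .80 power and the two-tailed level set in the same section.

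At stake is how a null result is read. A reader who accepts the statement will take a non-significant 6-month comparison as fair evidence against an effect of 0.65 SD, the level the article calls clinically interesting. The comparison is less sensitive than that.

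**Working it through.** **Inputs.** From the article: n = 30 per group, d = 0.65 SD, α = .05 two-tailed, power .80, t test. Not in the article: a loss rate. Losses of 10%, 20% and 30%, equal in both groups, are assumed to show a range.

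**Method.** Two-sample t test with n per group: df = 2n − 2 and noncentrality d√(n/2). Power is the probability that the noncentral t exceeds the critical value.

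**Step 1: reproduce the plan's figure.** The noncentrality is 0.65 × √(30/2) = 0.65 × 3.873 = 2.517.

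- Two-tailed: the normal approximation is Φ(2.517 − 1.960) = Φ(0.557) = 0.711. The noncentral t gives **0.697**.
- One-tailed: the normal approximation is Φ(2.517 − 1.645) = Φ(0.872) = 0.809. The noncentral t gives **0.800**.

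The effect detectable with .80 power at 30 v 30 is 0.736 SD two-tailed (normal approximation (1.960 + 0.842) × √(2/30) = 0.723) and 0.650 SD one-tailed. So the stated 0.65 SD is reproduced only by a one-tailed test. Two-tailed, .80 power at 0.65 SD needs 39 analysed per group.

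**Step 2: add loss.**

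| Loss | n per group | Two-tailed power at 0.65 SD | One-tailed power at 0.65 SD | Two-tailed effect with .80 power |
|---|---|---|---|---|
| 0% | 30 | 0.697 | 0.800 | 0.736 SD |
| 10% (assumed) | 27 | 0.650 | 0.762 | 0.777 SD |
| 20% (assumed) | 24 | 0.597 | 0.717 | 0.826 SD |
| 30% (assumed) | 21 | 0.538 | 0.665 | 0.886 SD |

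There is no slack even on the one-tailed scale: losing one family per group (29 v 29) gives 0.788. The two-tailed figure is then 0.682.

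**Step 3: separate the two parts.**

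- Sidedness, no loss: power at 0.65 SD falls from 0.800 to 0.697, or 10.3 points. The detectable effect rises from 0.650 to 0.736 SD, or 0.086 SD.
- Attrition, two-tailed: power falls a further 4.7 points at 10% loss (0.697 − 0.650), 10.0 at 20% (0.697 − 0.597) and 15.9 at 30% (0.697 − 0.538). The detectable effect rises a further 0.041, 0.090 and 0.150 SD.

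The sidedness part exceeds the attrition part at 10% loss and about equals it at 20%.

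**The case against.** **Attrition is not the main cause.** A reader might infer that .80 power at 0.65 SD would hold if every questionnaire came back, and that loss is what breaks it. The documents do not support this: under the two-tailed rule the figure is missed with no loss at all. This objection stands, and loss is a second shortfall added to the first.

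**.80 power is not unreachable.** A reader might also infer that any loss puts .80 out of reach. It is out of reach only for the effect quoted. Two-tailed, .80 is still reached at 0.78 SD with 10% loss and at 0.83 SD with 20%.

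**The size of the loss is unknown.** The right to withdraw is standard ethics wording and is not evidence of dropout. Families are allocated only after returning consent and T1, which screens out those who never respond. The later offer of the program to controls, and the DVD given to all after T3, may help retention. All this stands, which is why the loss rates are labelled as assumptions. In the other direction, follow-up is by post over six months, recruitment includes nurses in palliation, and a child can stop answering when the parent does not. Assuming no loss at all is therefore optimistic.

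**The analysis may do better than a t test.** Regression and SEM are also named, and T1 scores exist. With baseline adjustment the effective effect is 0.65/√(1 − r²). At an assumed baseline–follow-up correlation r = 0.5, two-tailed power is 0.816 at 30 per group, 0.772 at 27 and 0.721 at 24. At r = 0.6 it is 0.872, 0.834 and 0.787. The gain could be real, but the article gives no r and bases its power statement on t tests.

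**A condensed article may leave a loss rate to the full protocol.** That is fair as to the rate. It does not rescue the printed statement, which puts the recruited number in the place of the compared number and gives a detectable effect that its own test level does not yield.

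**Conclusion.** The point holds in two parts. With 30 v 30 and the article's own two-tailed .05 level, power at 0.65 SD is about 0.70, not .80, and the .80-power effect is 0.74 SD. This part needs no assumption beyond the t test that the article names. Because 30 per group is also the number recruited, nothing is allowed for loss. At losses of 10–30%, which are assumed, two-tailed power at 0.65 SD is about 0.65 to 0.54 and the .80-power effect is 0.78 to 0.89 SD.

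The power statement names no time point. That it applies to T2 and T3 follows from T1 being collected before allocation. The match with a one-tailed calculation is arithmetic; the article does not say that one was used. Nor does any of this show that the trial must enrol more families. It shows that the stated sensitivity is too favourable and should be corrected.

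**What to change.** Replace the single figure, in the power section and correspondingly in the Abstract, with a two-tailed statement for the number expected to be analysed at T3:

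- With no loss (30 v 30), the effect detectable with .80 power is 0.74 SD; power at 0.65 SD is about 0.70.
- With a stated expected loss, give the larger value, for example 0.83 SD at 24 v 24 if 20% are lost.
- Give the figure separately for parents and children, based on return rates observed so far. Enrolment began in January 2014, so some families should already be past T3, although the article does not report their returns.
- Show the two parts of the change separately: 0.65 to 0.74 SD is the sidedness correction, and 0.74 to 0.83 SD in the example is attrition. If sidedness is corrected elsewhere, it should not be counted twice.
- If a baseline-adjusted analysis is to be relied on for power, say so and state the assumed correlation.

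The cost is a few rewritten sentences and a less favourable figure. No extra enrolment, procedures or data collection are needed.

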**Methods:**

A randomized controlled trial (RCT) in which families (N=60) living with parental cancer will be randomized to either an intervention group or a control group. The intervention will last for 3 hours and includes (1) introduction, (2) psycho-education (living with cancer in the family and the importance of social network support), and (3) discussion (this family’s need for social support). Primary outcomes are social support, mental health, and quality of life, and secondary outcomes are resilience and parental capacity. Data will be collected by a set of questionnaires distributed to healthy parents (N=60) living with a partner with cancer, one child in the family between 8-18 years of age (N=60), and network members (N=210) of the intervention families at inclusion, and after 3 and 6 months. Comparing differences between the intervention group (n=30) and the control group (n=30), the power analysis shows that *P*<.05 and a statistical power = .80 would detect effect sizes of clinical interest.

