### Results

The Cancer PEPSONE study is ongoing, where enrollment of families began in January 2014. As of October 2015, 45 families are enrolled in the study. Of those families, 19 are randomized to the intervention group, with 15 families receiving the intervention together with approximately 120 network members, while 4 families are waiting for the intervention. As well, 20 families are enrolled in the control group and 6 families are not yet randomized. The first results from the study are expected in October 2015.

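### With 30 families per group and the plan's two-tailed P<.05, the effect detectable at 80% power is 0.74 SD, not about 0.65 SD; power at 0.65 SD is about 70%

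*Protocol article*

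**What the plan says.** All the inputs stand in one section of the Protocol article, under Power Calculations and Statistical Analyses.

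- The comparison is between "the intervention group (n=30) and the control group (n=30").
- For that comparison, "the power analysis showed that with *P*<.05 and a statistical power = .80", effects can be detected in t "tests of about 0.65 of one standard deviation or higher". This sentence does not say whether the alpha is one-tailed or two-tailed.
- The text then interprets the figure: "This means an ability of detecting effects sizes of medium size or higher", with a reference to Cohen's criteria but no cut-off. It adds that this effect level was judged clinically interesting and fitted the recruitment frame and the budget.
- The next paragraph sets the decision rule for the analyses: a two-tailed P "value of <.05 is considered to be statistically significant".
- The same paragraph names t tests and structural equation models for estimating the effect of the intervention, and multiple regression for exploring relationships and testing the research model.

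The Methods part of the abstract repeats the group sizes, P<.05 and power .80. It says that these "would detect effect sizes of clinical interest", without giving the effect size.

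**The concern.** The detectable effect depends on whether the test is one-tailed or two-tailed. The section fixes a two-tailed test, yet 0.65 SD looks too small for 30 per group on that basis.

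This is the only justification of sample size in the article, and the claim that the trial can find effects of clinical interest rests on it. If the figure is too favourable, the trial has less than its stated power at the effect it names. Readers of a null result could then overrate what it rules out.

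**Working it through.** **Inputs** (Protocol article, Power Calculations and Statistical Analyses): n = 30 per group, alpha = .05, power = .80, two-group t test, stated detectable effect 0.65 in SD units. The decision rule is two-tailed. No dropout allowance and no baseline correlation are given there, so all 60 families are taken as analysed and the test as unadjusted.

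**Formulas.** Normal approximation: detectable d = (z_alpha + z_power) × √(2/n). Exact: the two-sample t statistic has 2n − 2 = 58 degrees of freedom and noncentrality d × √(n/2) = d × √15; solve for the d that gives power .80.

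**Step 1: reproduce the stated 0.65.** It is reproduced with a one-tailed alpha.
- Normal approximation: (1.645 + 0.842) × √(2/30) = 2.487 × 0.2582 = 0.642.
- Noncentral t: d = 0.650. Power at d = 0.65 is 80.0%, and the n required is 29.97 per group.

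**Step 2: apply the two-tailed rule.**
- Normal approximation: (1.960 + 0.842) × √(2/30) = 2.802 × 0.2582 = 0.723. Power at d = 0.65 is 71.1%.
- Noncentral t: d = 0.736. Power at d = 0.65 is 69.7%.

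| Test, 30 per group, alpha .05 | Detectable d at 80% power | Power at d = 0.65 |
|---|---|---|
| One-tailed t | 0.650 | 80.0% |
| Two-tailed t | 0.736 | 69.7% |

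**Step 3: size of the gap.**
- Effect size: 0.736 / 0.65 = 1.13, so the detectable effect is 13% larger than stated.
- Power at 0.65 SD: 80 − 69.7 = about 10 percentage points short. The risk of a miss is 30.3% where 20% is implied.
- Sample size: 80% power at 0.65 SD, two-tailed, needs 38.1, so 39 per group. That is 78 families, 18 more than the planned 60. This only measures the gap; it is not a proposal to enlarge the trial.

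**Step 4: the remark on medium effects.** The article gives no cut-off. If medium is assumed to start at d = 0.5, two-tailed power there is 47.8%.

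**Step 5: fewer families, as hypotheticals only.** With 45 families in all (22.5 per group on average) the two-tailed detectable effect would be about 0.85 SD. With 24 per group, a 20% loss that has no source in the article, it would be about 0.83 SD. Neither bears on whether 0.65 is right for 30 per group.

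**The case against.** Several defences deserve an answer.

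**The word "about", or an approximation formula.** Neither closes the gap. The normal approximation still gives 0.72 two-tailed, and rounding does not turn 0.72 or 0.74 into 0.65.

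**A more efficient analysis.** T1 questionnaires are returned before allocation, so a baseline-adjusted analysis is possible. It would reach 0.65 SD two-tailed if the correlation between T1 and follow-up were about 0.47 (analysis of covariance) or about 0.61 (change scores). But the power sentence refers to t tests and states no correlation. This softens the practical consequence without rescuing the figure. Choosing 0.47 in order to keep 0.65 would fit the assumption to the answer.

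**The medium-size sentence may be right.** This has force. The sentence can be read as classifying the value just given: if 0.5 is the threshold, then 0.65 and 0.74 both lie above it. A reader might infer a second arithmetic error, but the article gives no cut-off, and the 48% power at 0.5 refutes only the stricter reading that every effect from 0.5 upward is covered at 80%. The sentence is loose rather than shown to be false.

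**How 0.65 was obtained.** A reader might conclude that the authors ran a one-tailed test. The numerical match is close, but the power sentence gives no sidedness, so this remains an inference.

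**Shrinking enrolment.** A reader might also take the Results section ("As of October 2015, 45 families are enrolled in the study") together with Table 1, which ends enrollment in Spring 2015, to mean that the trial will finish with 45 families. The article does not say so. The same section calls the study ongoing, with 6 families not yet randomized, so 45 is an interim count.

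**Conclusion.** The stated power figure is wrong as written. Under the two-tailed P<.05 set in the same section, 30 families per group give 80% power for 0.74 SD, and about 70% power for 0.65 SD. This assumes an unadjusted two-sample t test, equal groups and complete data from all 60 families; any loss of data would lower the power of that test further.

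The consequence is limited but real: the only sample-size justification overstates power by about 10 percentage points at the effect judged clinically interesting. It does not follow that the medium-size sentence is a second miscalculation, that a one-tailed test is planned, or that the trial will end short of 60 families.

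**What to change.** Keep the two-tailed test and 30 per group. Do not move to a one-tailed test to preserve 0.65. Then:

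1. Replace the power statement with: with 30 per group and two-tailed alpha .05, power is .80 for d=0.74 and about .70 for d=0.65.
2. Reword the medium-size sentence so that it does not imply 80% power across the whole medium range. If a cut-off of 0.5 is adopted, name it and give the power there, about .48.
3. Carry the restated figure into the claim, here and in the abstract, that this sample size detects effects of clinical interest. Say whether 0.74 SD is still the level meant.
4. Show figures for fewer families, such as 0.85 SD with 45 families or 0.83 SD with 24 per group, only as labelled hypotheticals.

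This costs a change of wording and a less favourable stated figure. Recruitment, tests and conduct stay as they are.

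### The stated detectable effect of about 0.65 SD at .80 power does not hold under the plan's own two-tailed .05 rule; for an unadjusted t test on all 60 families it is about 0.74 SD

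*Protocol article*

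**What the plan says.** The section Power Calculations and Statistical Analyses compares two arms of 30 and reports: "the power analysis showed that with *P*<.05 and a statistical power = .80", the detectable effects are those in t "tests of about 0.65 of one standard deviation or higher". It calls this medium size or higher by Cohen's criteria, and then adds: "This effect level was judged to be of clinical interest, and was within the study’s recruitment frame and economy". The power sentence does not say whether its test is one- or two-tailed.

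The following paragraph of that section fixes the significance rule: "A two-tailed *P* value of <.05 is considered to be statistically significant". For estimating the effect it says that different methods, such as t "tests and structural equation (SEM) analyses will be used".

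The Methods part of the abstract repeats the arm sizes, the P<.05 threshold and the .80 power, and says that these "would detect effect sizes of clinical interest". It gives no figure in SD units.

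**The concern.** The power statement prints all the inputs needed to check it except sidedness, and the next paragraph supplies that. With 30 per arm, a two-tailed test at .05 and power .80, the familiar value for a two-sample t test is above 0.7 SD, so 0.65 looks too favourable.

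This figure, with the practical remark on recruitment and economy, is the only sample-size justification the article gives. If it is wrong under the stated rule, readers of the plan and of the results will credit the trial with more sensitivity than its t test has.

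**Working it through.** **Inputs, all from Power Calculations and Statistical Analyses**
- n = 30 per arm, so df = 30 + 30 − 2 = 58.
- α = .05, and power = .80.
- Test: two-sample t test, because the figure is tied to t tests.
- Stated detectable effect: d ≈ 0.65 SD.
- Criterion for the analysis: two-tailed.

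**Formula.** For a standardised difference d, the t statistic follows a noncentral t distribution with 58 df and noncentrality d / √(1/30 + 1/30) = d / √(2/30) = d / 0.2582. Power is the probability that this variable exceeds the critical value, plus the negligible opposite tail for a two-sided test. The detectable effect is the d at which power equals .80. As a cross-check, the normal approximation is d = (z for α + z for power) × √(2/30).

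**Step 1: reproduce the plan's figure.** A one-sided .05 test (equivalently, two-sided .10) gives:
- exact detectable effect 0.6496 SD;
- normal approximation (1.645 + 0.842) × 0.2582 = 0.642 SD;
- exact power at 0.65 SD of 0.800;
- smallest n for .80 power at 0.65 SD: 30 per arm.

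This matches the printed effect, power and sample size together.

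**Step 2: apply the stated two-tailed .05 rule.** The same calculation gives:
- exact detectable effect 0.7356 SD;
- normal approximation (1.960 + 0.842) × 0.2582 = 0.723 SD;
- exact power at 0.65 SD of 0.697 (normal approximation 0.711);
- smallest n for .80 power at 0.65 SD: 39 per arm, or 78 families (normal approximation 38 per arm). This is given for scale only.

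**Step 3: size of the gap.** 0.7356 / 0.65 = 1.13, so the detectable effect is 13% larger than stated. The type II error at 0.65 SD is 1 − 0.697 = 0.303, against the 0.20 implied.

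**Step 4: could baseline adjustment explain 0.65?** Reaching 0.65 SD two-sided needs the SD to shrink by the factor 0.65 / 0.7356 = 0.8836.
- Under ANCOVA the factor is √(1 − ρ²), so ρ = √(1 − 0.8836²) = 0.47.
- For a change score the factor is √(2(1 − ρ)), so ρ = 1 − 0.8836²/2 = 0.61.

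The article gives no baseline-to-follow-up correlation and mentions no adjustment in the power sentence.

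**Step 5: sensitivity to loss.** The 0.74 SD assumes that all 60 families are analysed. The article states no loss rate. As assumptions for illustration, 10% loss (27 per arm) gives 0.78 SD and 20% loss (24 per arm) gives 0.83 SD, both two-sided at .80 power.

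**The case against.** Several points can fairly be made for the plan.

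- **The cause is not documented.** A reader might infer that the power calculation was one-tailed. The numeric match is close, but the article never states the sidedness of that calculation, so this remains an inference. The mismatch with the two-tailed rule stands whatever its cause.
- **A more efficient analysis might reach 0.65 SD.** Outcomes are collected at inclusion and at 3 and 6 months, and the methods listed are open-ended, so the unadjusted t test is not fixed as the only or primary analysis. A reader should therefore not take 0.74 SD as the sensitivity of the whole trial. It belongs to the unadjusted t test. Still, the printed 0.65 is explicitly a t-test figure and no correlation is given, so adjustment does not account for it.
- **The word about.** It allows for rounding, but 0.74 does not round to 0.65.
- **The abstract.** A reader might think that it repeats the wrong number. It does not, because it makes only a general claim about effects of clinical interest.
- **Clinical interest.** A reader might conclude that the trial can no longer detect what was judged worthwhile. The text does not settle this. The phrase about clinical interest follows the sentence on medium size or higher and may refer to that band, in which 0.74 SD also falls.
- **Consequences.** The slip biases no estimate and does not inflate the type I error, and the sample was also set by practical limits. This supports a correction of wording, not a change of design.

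**Conclusion.** The point holds in limited form. Under the section's own two-tailed .05 criterion, the statement that 30 v 30 gives .80 power at about 0.65 SD is wrong for the t test it names. The correct values are about 0.74 SD at .80 power and about .70 power at 0.65 SD. They rest on an unadjusted two-sample t test, equal arms and all 60 families analysed, so they are a best case for that test if families are lost.

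The arithmetic is firm; the one-tailed origin of the 0.65 is probable but not stated. It would go too far to make 0.74 SD a benchmark for judging null results: it presupposes complete data and one particular analysis, and a confidence interval shows directly which effects the data exclude.

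**What to change.** Keep the sample size and two-tailed testing. In Power Calculations and Statistical Analyses, replace the power sentence with wording such as: *With 30 v 30 families analysed, two-tailed P<.05 and power .80, an unadjusted t test detects about 0.74 SD; power at 0.65 SD is about .70.* Check that the following remark on clinical interest still says what is meant beside the new figure.

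In the abstract there is no number to correct; make its general claim consistent with the revised sentence. Interpret null results from confidence intervals.

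If the 0.65 did come from a baseline-adjusted calculation, the alternative is to say so and print the assumed correlation.

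The cost is about two sentences and a slightly less favourable figure. Recruitment, data collection and analysis do not change.
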